**Methods:**

This is a mono-centre randomized clinical trial with three parallel groups: (1) SPSP, (2) APT, (3) ST. Randomization on patient level will be pre-stratified according to type of PD. The total study population to be included consists of 264 patients with Cluster-C PDs or other specified PD with mainly Cluster-C traits, aged 18–65 years, seeking treatment at NPI, a Dutch mental health care institute specialized in PDs. SPSP, APT and ST (50 sessions per treatment) are offered twice a week in sessions of 50 min for the first 4 to 5 months. After that, session frequency decreases to once a week. All treatments have a maximum duration of 1 year. Change in the severity of the PD (ADP-IV) will be the primary outcome measure. Secondary outcome measures are personality functioning, psychiatric symptoms and quality of life. Several potential mediators, predictors and moderators of outcome are also assessed. The effectiveness study is complemented with a cost-effectiveness/utility study, using both clinical effects and quality-adjusted life-years, and primarily based on a societal approach. Assessments will take place at baseline, start of treatment and at 1, 3, 6, 9, 12, 18, 24 and 36 months.

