## Introduction

### Background and rationale {6a}

Personality disorders (PDs) are complex mental health disorders associated with low levels of quality of life, high health care costs, and poor prognosis. PDs are clustered in three clusters: A, B and C (DSM-V, [3]). Cluster-C PDs, including avoidant, dependent and obsessive-compulsive PDs, are among the most common mental disorders in the general population, with reported prevalence rates of 3–9% [64, 94]. See Table 1 for brief definition of the clusters. In clinical populations, this cluster of PDs is most prevalent [4] and is associated with high levels of burden, societal dysfunctioning, low quality of life [89] and chronicity of many other common mental health disorders [73, 80]. Research in the field of PD has, to date, mainly excluded the Cluster-C PDs and focused on borderline PDs. Also, Cluster-C PDs are generally not included in international guidelines for PDs [49]. This means that a large group of patients has been neglected, and knowledge on how to treat them is lacking.

**Table 1 Tab1:** Brief definition of Cluster-A, B and C PDs

Cluster-A PDs (paranoid, schizoid and schizotypal PD) are considered to be the odd, eccentric disorders.	
Cluster-B PDs (borderline, narcissistic, histrionic, antisocial PD) are characterized by thoughts and emotions that are dramatic and overly emotional.	
Cluster-C PDs (avoidant, compulsive, dependent PD) are characterized by anxiety and fear (DSM-V, APA, 2013).	

Despite the scarcity of outcome studies, in routine clinical practice patients with (comorbid) Cluster-C PDs are frequently referred to mental health care and offered general treatments such as cognitive behavioural therapy or psychodynamic therapy. In order to obtain more evidence, this study compares the differential effectiveness of three individual psychotherapies for Cluster-C PDs: short-term psychodynamic supportive psychotherapy (SPSP), affect phobia therapy (APT) and schema therapy (ST).

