### Objectives {7}

The primary aim of this study is to compare the effectiveness and cost-effectiveness of the three individual treatments (SPSP, APT and ST) for Cluster-C PDs. The primary outcome of this superiority study is the severity of Cluster-C PD. We will compare the slopes over time of the three treatments from 0 to 12 months, with assessments of Cluster-C PD severity taking place at baseline, 1, 3, 6 and 9 months. Additionally, we will research differences between the outcomes of the three treatments at 18, 24 and 36 months follow-up. No hypothesis was formulated about the direction of a difference.

The second aim of this study is to explore working mechanisms by focussing on therapy-specific factors in the context of the contribution of common factors across psychotherapies. Selected therapy-specific factors are as follows: therapy-specific interventions; insight for SPSP; change in affect, defence style, perception of the self for APT; change in schema modes for ST. Working alliance is the non-specific factor being investigated.

The third aim is to identify general and specific predictors. Potential moderators will be studied exploratively. Firstly, we hypothesize that patients with relatively more childhood trauma will benefit more from ST than SPSP and APT, because of the use of imaginary rescripting, an evidence-based trauma processing technique [35, 83]. Secondly, we expect that patients with more severe personality pathology (e.g. borderline personality organization (Kernberg, [57]) will profit more from ST or SPSP than APT. This is because these therapies are developed and have proven their effectiveness for a broader range of PDs [60, 88], whereas APT is originally designed for the Cluster-C/neurotic population [25].

The relationship between specific treatment interventions, mediators and outcome will also be explored. Therapists will indicate per session which of the core interventions per treatment they have applied in their sessions. The hypothesis is that certain interventions will be stronger connected to mediators and outcome than others. For example, experiential techniques (imagery rescripting, multiple chair technique) for ST; adequate support for SPSP; facilitation of expression of emotions for APT.

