#### Primary outcome measure

Assessment of DSM-IV Personality Disorders questionnaire (ADP-IV, [87]). The primary outcome is the severity of Cluster-C personality pathology, measured by the ADP-IV. The ADP-IV is a self-report questionnaire, assessing DSM-IV PD criteria. Patients indicate on a 7-point Likert scale to what degree PD criteria hold for them, ranging from 1 (‘not at all’) to 7 (‘completely’), and whether they experience distress from it (on a range from 1—not at all to 3—definitely). Item construction of the ADP-IV allows for both dimensional and categorical diagnostic evaluation [87]. Adequate internal consistency, validity and reliability were shown consistently in previous studies [30, 85].

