## Statistical methods^7^

### Statistical methods for primary and secondary outcomes {20a}

#### Primary study parameter(s)

##### Treatment response: ADP-IV

All analyses will be conducted according to the intention-to-treat principle. Primary and secondary outcomes are analysed with Linear Mixed Models, with random effect of site (if estimation allows). The primary outcome measure is the change in the total ADP-IV score using the dimensional scoring algorithms [86]. Change in the primary outcome measure and the relative effectiveness of the three treatments will be analysed using mixed regression so that all available data are used, and taking into account the levels of participant and time. The addition of random levels for therapist, to adjust for possible therapist effects, will be tested. The underlying distribution of the mixed regression model will be determined based on the distribution of residuals (e.g. normal, gamma, negative binomial). Per-protocol analyses will also be conducted to test for robustness and sensitivity.

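### The protocol names two different primary outcomes: Cluster-C severity in the objectives and outcome sections, and the total ADP-IV score in the analysis section

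*Protocol article*

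**What the plan says.** Four places in the protocol article describe the primary outcome.

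- Objectives {7}: "The primary outcome of this superiority study is the severity of Cluster-C PD".
- Outcomes {12}, Primary outcome measure: "The primary outcome is the severity of Cluster-C personality pathology, measured by the ADP-IV".
- Statistical methods {20a}, Treatment response: ADP-IV: "The primary outcome measure is the change in the total ADP-IV score using the dimensional scoring algorithms".
- Abstract, Methods: "Change in the severity of the PD (ADP-IV) will be the primary outcome measure". This names the instrument but no score.

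The instrument itself is introduced with "The ADP-IV is a self-report questionnaire, assessing DSM-IV PD criteria". The moderator, mechanism and cost-effectiveness paragraphs name the ADP-IV as their outcome without saying which score. The last paragraph under Cost-effectiveness says that the statistical analyses described there are still being developed and that the best method will be chosen when the analyses are done.

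**The concern.** The analysis section is the only place that says how the primary outcome is scored, and the score it names is not the construct in the objectives and outcome sections. A statistician who follows the analysis section tests overall personality pathology. One who follows the objectives tests Cluster-C pathology. Both could claim to follow the protocol, and they could reach different conclusions.

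Two things are at stake. The confirmatory test may not answer the stated question. And with two scores available from one questionnaire, the choice could be made once results are known. The Bonferroni level of 0.0167 pays for three pairwise treatment comparisons, not for two candidate outcomes.

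**Working it through.** **1. Do any other passages settle it?** No. The abstract and the secondary analyses are neutral between the two scores. The analysis section refers to dimensional scoring algorithms in a cited source, which separates dimensional from categorical scoring but does not limit the total to Cluster C.

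**2. Could the two scores coincide?** Only if the total covered Cluster-C items alone, which the article does not say. Table 1 lists three disorders in Cluster A ("Cluster-A PDs (paranoid, schizoid and schizotypal PD"), four in Cluster B ("Cluster-B PDs (borderline, narcissistic, histrionic, antisocial PD") and three in Cluster C ("Cluster-C PDs (avoidant, compulsive, dependent PD"). If the total spans all ten, 7 of 10 lie outside Cluster C. This is a count of disorders, not of ADP-IV items, which the article does not give.

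**3. The protocol's own sample size.** Inputs from Sample size {14}: f = 0.11, two time points, correlation 0.60, alpha 0.0167, power 0.80.

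- f(V) = 0.11 × √(2 / (1 − 0.60)) = 0.2460
- d = 2 × 0.2460 = 0.492
- Noncentral F with N = 176: λ = 0.0605 × 176 = 10.65, df 1 and 174, power 0.800

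The stated 88 per arm is reproduced. The calculation uses a standardised effect and names no ADP-IV score.

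**4. Can the choice of score matter?** This is an illustration, and its assumptions are not in the document: ten disorder scales with equal variance of change, common correlation r between scales, and d = 0.492 on the sum of the three Cluster-C scales. Let h be the standardised treatment effect on each A/B scale relative to that on each C scale. Then

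d(total) = 0.492 × [(3 + 7h) / √(10 + 90r)] / [3 / √(3 + 6r)]

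At r = 0.5 and h = 0.5: (6.5 / 7.416) / (3 / 2.449) = 0.716, so d(total) = 0.352 and power is 0.47.

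Power on the total score, 88 per arm, alpha 0.0167:

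| h | r = 0.3 | r = 0.5 | r = 0.7 |
|---|---|---|---|
| 0 | 0.11 | 0.09 | 0.09 |
| 0.25 | 0.29 | 0.24 | 0.22 |
| 0.5 | 0.55 | 0.47 | 0.42 |
| 1 | 0.93 | 0.88 | 0.84 |

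The total matches the Cluster-C score when h = [3√((10 + 90r) / (3 + 6r)) − 3] / 7, which is 0.76, 0.87 and 0.94 at r = 0.3, 0.5 and 0.7.

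**5. Sensitivity to the equal-variance assumption.** If the change on A/B scales has half the SD of that on C scales (r = 0.5), power at h = 0, 0.25 and 0.5 is 0.22, 0.39 and 0.58. At a quarter of the SD it is 0.42, 0.55 and 0.67. The loss shrinks as the A/B scales vary less.

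**The case against.** The strongest reply is that the damage is unproven. The article gives no ADP-IV scale list, item counts or baseline scores, and its scoring source is cited but not shown. The all-disorder reading of the total is the natural one, but not the only one possible.

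A reader might infer that the total is dominated by disorders the trial excludes, and that those items have little room to improve and mainly add noise. The exclusion of full and subthreshold Cluster-A and B disorders makes this plausible. It does not show that patients score at the floor on those self-report items. The inference also sits badly with large power losses, because items that barely move would also vary less and weigh less in a sum.

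A reader might also infer that the effect the trial was sized for is diluted. That would require d = 0.492 to have been set on the Cluster-C score, and the sample size section ties it to no score. If it was meant for the total, nothing is diluted. If treatment differences on A/B traits are close to those on C traits, the total is the more powerful score.

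All of this stands against a claim about size or direction. It leaves the contradiction untouched. Nor can the contradiction be left to a separate analysis plan, since any plan would have to depart from one part of this article.

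**Conclusion.** The point holds as an unreconciled definition of the primary endpoint, and it must be fixed because the confirmatory test is otherwise undefined. The conflict rests on the text alone and needs no assumptions.

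The power range of about 0.1 to 0.9 shows only that the choice of score can matter. It depends on the assumed scales, correlations and relative effects, and the document does not fix its direction. The 88 patients per arm follow correctly from the stated inputs and need no change on this account.

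**What to change.** Before any comparison by arm, name one score in the same words in the abstract, the Objectives, the Primary outcome measure section and the statistical section. The Cluster-C dimensional score is the one that matches the stated objective and outcome. In Treatment response: ADP-IV, replace the total score with it and make the total a secondary outcome. The sponsor could keep the total as primary, but would then have to rewrite the objective and the outcome definition.

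Also state which score d = 0.492 refers to, and which ADP-IV score is used in the moderator, mechanism and cost-effectiveness analyses.

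The cost is an amendment to wording. The ADP-IV is already administered, so no new data are needed, and the sample size stands if d = 0.492 is retained for the chosen score.

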#### Therapists

All therapists in this trial are qualified psychologists or psychiatrists with additional training in SPSP, APT or ST for Cluster-C PDs. For ST therapists, a junior registration of the Dutch association of ST is requested (general course in ST and a minimum of 20 supervisions). For APT and SPSP therapists, a general course in APT or SPS is required, and in addition a minimum of 3 months supervision and approval of competence from the supervisor. Next, participating therapists will be trained in the specific Cluster-C protocols prior to the start of the trial. Biweekly peer supervision groups are organized to maintain therapy quality. We expect to include 20 therapists per treatment (SPSP, APT and ST). All therapists will receive a unique code.

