### Participant timeline {13}

#### Sample size {14}^3^

First, the required sample size was calculated to compare the three types of active treatments. Three pairwise comparisons will be conducted between the active treatment arms (ST vs. APT, ST vs. SPSP; APT vs. SPSP). We want to detect a medium effect size (*f*=0.11) in a pairwise comparison of pre-post change between two active treatment arms, equivalent to *f*(*v*)=.2460 and Cohen’s *d*=.492, with Bonferroni-corrected *p* = 0.0167, a power of 0.80 and within-person correlation coefficient=0.60, for which 88 patients are needed per arm. Because three types of therapies will be compared, 3 × 88 = 264 participants are needed to perform three pairwise comparisons. We chose a medium effect size (f=0.11^4^) since this would also be a clinically meaningful difference, as opposed to a smaller effect size.

The correlation of 0.60 is an educated guess of the correlation between repeated assessments based on the previous RCTs the authors conducted.

The final analysis will be conducted with mixed regression on time series: the change in slope over time between two treatments. Because power analysis for mixed regression are complex and based on complex assumptions about the covariance-structure, a simplified approach was chosen by conducting a power analysis on the pre-post change.

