##### Cost-effectiveness

The cost-effectiveness analysis (CEA) will be conducted from a societal perspective. Within the CEA, the difference in societal costs (measured by the TiC-P at baseline and after 6, 12, 18, 24 and 36 months) generated by patients in the three treatments will be related to the difference in clinical effects (measured with the ADP-IV and quality-adjusted life-years based on the EQ-5D-5L) over the course of 36 months. Missing cost and effect data will be imputed using multiple imputation. Mixed model regression analyses will be used to estimate cost and effect differences between groups. Bootstrapping with 5000 replications will be used to estimate 95% confidence intervals around cost differences and the uncertainty surrounding the incremental cost-effectiveness ratios (ICERs). Uncertainty surrounding the ICERs will be graphically presented on cost-effectiveness planes. Cost-effectiveness acceptability curves [36] will also be estimated. Adjustment for confounders and effect modifiers will be done if necessary.

The statistical analyses described above are still under development and examples of possible methods. At the time of the analyses, we will use the optimal method for analysing the data.

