### Limitations

There are several limitations to consider. First, in the design of the study, no inactive control group was added. This means that the influence of the natural course of variation over time cannot be ruled out. We did not include a no-treatment comparison group due to ethical issues involved in withholding treatment for this population seeking specialized PD care.

Second, by including a wide range of patients, Cluster-C PDs and the group of patients with an otherwise specified PD diagnosis, the sample might be more heterogeneous than in studies only including full Cluster-C PDs. However, the inclusion criterion of a predominance and a minimum of five Cluster-C traits and the exclusion of (subthreshold) cluster-A and B PD, ensures that patients with predominantly Cluster-C pathology are included. By adding the otherwise specified PD patients, we expect to better adapt to the clinical practice, where the prevalence of full Cluster-C diagnosis is less common than mixed Cluster-C diagnosis.

Third, we did not adjust the sample size for dropout, which might have a negative impact on the power. However, we expect mixed regression with multiple measurements between pre- and posttreatment will compensate for the potential loss of power due to dropout.

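### Therapist adjustment in the primary model depends on a preliminary test, and the sample size takes patients as independent; if therapist effects on change exist, the pairwise error exceeds 0.0167 modestly and power is below 0.80

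*Protocol article*

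**What the plan says.** All places are in the protocol article.

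- *Treatment response: ADP-IV*: the primary outcome is analysed by mixed regression "taking into account the levels of participant and time". Therapist is handled differently: "The addition of random levels for therapist, to adjust for possible therapist effects, will be tested". No test, threshold or default is named.
- *Therapists*: "We expect to include 20 therapists per treatment (SPSP, APT and ST"). Therapists hold additional training in one of the three therapies, and each receives a unique code.
- *Sample size*: each of three pairwise comparisons is sized on pre-post change with Cohen's d = 0.492, "with Bonferroni-corrected *p* = 0.0167, a power of 0.80 and within-person correlation coefficient=0.60, for which 88 patients are needed per arm". No therapist ICC or design effect appears. The section calls the pre-post basis a simplification of the mixed regression that will be used.
- *Objectives*: the treatments are compared on slopes over time, and "No hypothesis was formulated about the direction of a difference".
- *Limitations*: dropout is named as a threat to power. Therapist clustering is not.

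**The concern.** Patients treated by the same therapist may change more alike than patients of different therapists. Because therapists are recruited and trained per treatment, this similarity lies within arms. It adds to the variance of every difference between arms.

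On its natural reading the plan keeps the therapist level only if a test supports it. A variance test with four or five patients per therapist has little power against a small or moderate effect, so a non-significant result is weak evidence of no clustering. If a real effect is dropped, standard errors are too small and the Bonferroni level for that comparison is not held. In a head-to-head trial, that means a higher chance of declaring one therapy better when it is not.

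The form of the term also matters. The contrast of interest is change. If baseline is one of the outcome rows, a therapist intercept alone largely cancels out of that contrast, since therapists cannot affect scores taken before treatment. The text speaks only of random levels and does not say where the therapist effect would act.

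Separately, the stated power of 0.80 rests on independent patients.

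**Working it through.** **1. Reproduce the stated sample size.** Inputs from *Sample size*: f = 0.11, within-person correlation 0.60, alpha 0.0167 (0.05/3), power 0.80. Two-sided testing is taken because no direction is hypothesised and because only two-sided testing reproduces 88: the normal approximation needs 87 per arm two-sided and 73 one-sided.

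- f(V) = 0.11 × √(2/(1 − 0.60)) = 0.2460, and d = 2 × 0.2460 = 0.492. Both match the text.
- Noncentral t with 2n − 2 degrees of freedom: power is 0.795 at 87 per arm and 0.8005 at 88.

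So 88 is exact for independent patients. There is no margin and no therapist term in it.

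**2. Caseload.** 88/20 = 4.4 patients per therapist.

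**3. Performance of testing, then dropping.** The ICC is an assumption, as is the 5% test level. Pre-post change was simulated with 20 therapists per arm and, in the main runs, four or five patients each. The therapist variance was tested at 5%. If significant, a random-therapist comparison was used, otherwise a patient-level comparison. Ranges span different implementations: an F test or a REML likelihood-ratio test, and a variance test using two arms or all three.

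| Assumed ICC | Therapist effect detected | Pairwise error, test then drop |
|---|---|---|
| 0 | – | 0.016–0.017 |
| 0.02 | 9–11% | 0.018–0.020 |
| 0.05 | 20–26% | 0.021–0.026 |
| 0.10 | 46–60% | 0.023–0.026 |

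The target is 0.0167. Always including the therapist effect gave 0.013–0.017 over ICC 0.02 to 0.10. With uneven caseloads (1 to 14 patients per therapist) and ICC 0.05, testing then dropping gave about 0.029 and always including gave 0.016–0.019.

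**4. Power at 88 per arm with therapist always in the model.** Design effect DE = 1 + (4.4 − 1) × ICC; noncentrality = 0.492 × √(88/(2 × DE)); two-sided alpha 0.0167. Degrees of freedom come from therapists: 2 × 20 − 2 = 38 if two arms inform the variance, 3 × 20 − 3 = 57 if all three do.

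| Assumed ICC | DE | Noncentrality | Power, 38 df | Power, 57 df |
|---|---|---|---|---|
| 0.02 | 1.068 | 3.158 | 0.741 | 0.753 |
| 0.05 | 1.170 | 3.017 | 0.695 | 0.708 |
| 0.10 | 1.340 | 2.819 | 0.625 | 0.639 |

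Simulation with even caseloads agrees closely: 0.72–0.74, 0.69–0.70 and 0.62–0.63. With patient-level degrees of freedom (174) the formula gives 0.770, 0.725 and 0.656. Those values are too favourable for a model that carries a therapist effect.

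**The case against.** The case on the other side is substantial.

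- **Both harms need a therapist ICC above zero, and the documents give none.** This stands. At ICC zero the rule behaves correctly. At 0.01 the design-effect power with patient-level degrees of freedom is 0.785, a negligible loss.
- **A reader might infer that the test will usually miss a real effect.** That holds only for smaller ICCs. At 0.10 detection is 46–60%, and at 0.15 it is 72–86%.
- **A reader might infer a large inflation of error.** Ignoring therapist altogether would give about 0.039 to 0.041 at ICC 0.10, but the plan does not propose that. Under the conditional rule the excess is below one percentage point with even caseloads.
- **The 5% threshold is assumed.** The article names none, and a more liberal threshold would drop real effects less often. Nor does the article plan an intercept-only therapist term. If baseline is a covariate, an intercept on post-baseline scores does not cancel.
- **Random-effect structure is commonly left to the analysis plan,** which is not shown. Nor are the footnotes to the sample size and statistical methods sections. This limits any complaint about missing detail. It does not remove the point, because the article itself states a selection rule for the primary model, and unconditional inclusion holds the error better.
- **A reader might add dropout, or the remark that the optimal method will be chosen at analysis, to this point.** The documents disclose the missing dropout allowance openly, and the remark on methods reaches well beyond therapists. Both are separate matters and carry no weight here.

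**Conclusion.** The point holds in conditional form. The plan makes therapist adjustment depend on a test that is weak at 4.4 patients per therapist, and it sizes the trial as if patients were independent. For an assumed therapist ICC on change of 0.02 to 0.10, the pairwise type I error is about 0.018–0.026 against 0.0167. Power with therapist properly modelled is about 0.75 down to 0.63, before dropout.

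The documents do not support saying outright that the error rate is exceeded or that 80% power is missed, because they give no ICC. The power figures also rest on the pre-post simplification. Repeated assessments may recover some power in the final model by reducing within-patient noise, but they do not remove differences between therapists in change. Severity is moderate: the plan recognises therapist effects and records the codes needed to model them.

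**What to change.** In *Treatment response: ADP-IV*, replace the conditional sentence by a statement that the primary model includes a random therapist effect, nested in treatment and acting on change over time, regardless of its significance. This is a therapist-by-time effect if baseline is an outcome row, or a therapist effect on post-baseline scores if baseline is a covariate. Use therapist-level degrees of freedom for the pairwise comparisons.

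In *Sample size*, state that 0.80 at 88 per arm assumes a therapist ICC of zero. Give power on the same pre-post basis over an ICC range labelled as assumed: about 0.74–0.75 at 0.02, 0.70–0.71 at 0.05 and 0.63–0.64 at 0.10, before dropout.

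The cost is wording, somewhat wider intervals and a less favourable stated power. At ICC 0.05, simulated power is 0.69–0.70 with therapist always included, against 0.74–0.75 under the conditional rule, whose advantage comes partly from understated standard errors. If the true ICC is zero, the smaller degrees of freedom still cost a little: the same formula with DE = 1 gives 0.772 (38 df) to 0.785 (57 df). No new data are needed, since therapists are already coded. The change should be made before outcomes are analysed.
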